### Control

The control group will not receive the ASMP but will be sent an arthritis self-management book [2]. There is currently no evidence to suggest that provision of this book alone is beneficial, although to date, this has only been assessed in one study which investigated the effect of the ASMP for people with OA, rheumatoid arthritis or fibromyalgia [19]. After 4 months, no change in pain, self-efficacy, disability or mental health was observed for the control group which received the Arthritis Self-Help book only.

### Outcome measures

Participants will be assessed using a range of standardised, self-report measures which include:

#### 1. The Assessment of Quality of Life (AQoL) instrument

The primary outcome for this RCT is HRQoL at 12 months, as measured by the AQoL instrument. This outcome was chosen to reflect the potential longer-term benefits of the multi-faceted ASMP [6]. The AQoL instrument is an Australian generic utility tool which can be used for health economic evaluation through estimation of utilities and calculation of Quality-Adjusted Life Years (QALYs). The four dimensions covered by this instrument include Independent Living, Social Relationships, Physical Senses and Psychological Wellbeing. The AQoL instrument has strong psychometric properties and is more sensitive and responsive than many other widely-used scales including the Medical Outcomes Study 36-Item Short Form (SF-36) [20,21]. The AQoL utility score ranges from -0.04 (worst possible HRQoL) to 1.00 (full HRQoL). A minimal important difference for the AQoL instrument is considered to be between 0.03 and 0.08 AQoL units [22]. For the present study, an increase of 0.05 AQoL units will be regarded as a clinically important improvement in HRQoL.

#### 2. The Health Education Impact Questionnaire (heiQ)

The heiQ was developed to evaluate the intended effects of self-management programs and was found to be reliable and responsive to change in an Australian validation study [6,23]. It has since been administered to over 1300 Australians with chronic conditions who have attended self-management programs [24]. The heiQ contains 42 questions and covers 8 dimensions which include: Positive and active engagement in life, Health behaviour change, Skill and technique acquisition, Constructive attitudes and approaches, Self monitoring and insight, Health service navigation, Social integration and Emotional wellbeing. Each dimension produces an overall score from 1 (strongly disagree) to 6 (strongly agree).

#### 3. The Western Ontario and McMaster Universities OA (WOMAC) Index

The WOMAC Index is a disease-specific measure of health status and is widely used in OA research. The validity, reliability and responsiveness of this measure have been demonstrated in an extensive range of studies [25]. The WOMAC Index consists of 24 questions which cover pain, stiffness and fatigue and produces a total score which can be transformed to a 0 (best possible health) to 100 (worst possible health) scale. The pain subscale score will also be reported.

#### 4. The Kessler Psychological Distress Scale (K10)

The K10 instrument provides a measure of psychological distress [26] and is used in the World Health Organisation World Mental Health Survey and Australian population health surveys. High K10 scores representing high distress are strong predictors of affective disorders such as depression and anxiety [27]. The scale has demonstrated discriminant validity in United States National Health Interview Surveys [26]. The K10 consists of 10 questions about anxiety, depression and worry and produces a total score ranging from 10 (lowest psychological distress) to 50 (highest psychological distress).

#### 5. The Hip and Knee Multi-Attribute Priority Tool (MAPT)

The MAPT was designed as a measure of arthritis disease severity [28]. The MAPT was developed through extensive consultation with patients, orthopaedic surgeons and other health professionals. The MAPT contains 11 items which cover areas such as self-care, enjoyment of life, the economic impact of arthritis and deterioration. A validation study involving over 900 people with hip or knee arthritis demonstrated construct validity, good test-retest reliability and responsiveness to change [28]. The MAPT produces a score from 0 (least disease severity) to 100 (greatest disease severity).

#### 6. Health services use

The (self-reported) number of visits to health professionals during the previous month will be collected from all participants. The costs of consulting health professionals will be calculated using published prices for medical and allied health costs. Additionally, if specific consent is provided, Australian Health Insurance Commission data will also be obtained regarding the use and cost of prescription medications, medical consultations, pathology tests and hospitalisations during the study period.

#### 7. Community services use

Information about the use of both paid and unpaid community assistance (for example, home help and Meals on Wheels) will also be collected by postal survey.

### Follow-up procedures

Participants will receive follow-up questionnaires at 6 weeks (heiQ and MAPT instruments only), 3 months (full range of instruments) and 12 months (full range of instruments). Reply-paid envelopes will be provided to maximise response rates. At each follow-up assessment, participants will be asked whether they have attended an Arthritis Self-Management Program since entering the study to detect potential cross-over from the control group.

### Qualitative component

Recent research suggests that questionnaire-based outcome assessment may not accurately reflect people's experiences of chronic disease self-management [29,30]. Given these findings, this study will incorporate an additional qualitative component to corroborate the questionnaire-based data collected and to elicit detailed information about participants' expectations of the ASMP and perceived outcomes following the program. A subgroup of 100 participants will be selected for the qualitative component. A Solomon four-group design will be used to minimise the potential impact of behavioural changes prompted by the interviews [31,32]. This design incorporates two groups of participants who do not undergo a baseline interview, allowing both the potential effect of the intervention *and *the potential effect of the interview to be evaluated. As illustrated in Figure 1, 50 participants will undergo both baseline and 6 week interviews (25 participants from the intervention group and 25 participants from the control group). A further 50 participants (25 from the intervention group and 25 from the control group) will undergo interviews at 6 weeks only. The semi-structured telephone interviews (approximately 1 hour in duration) will be conducted by two researchers trained in qualitative interview techniques.

The qualitative interviews may also reveal the presence of 'response shift', a potential change in perspective as a result of attending the ASMP [30,33]. Response shift has been purported to confound the traditional pre-post assessment methods used to evaluate the outcomes of health care interventions. In the context of self-management education programs, response shift may arise when a person re-evaluates themselves after a program (retrospectively) as being better or worse *before *the course than they had thought. Response shift can be categorised as negative (when a person realises they were worse before the course than they had first thought) or positive (when a person realises they were better before the course than they had first thought). In a study of 39 people who completed an arthritis or chronic disease self-management program, Osborne et al [30] found that 31% experienced a negative response shift, while 20% experienced a positive response shift. The effect of this change in perspective on outcomes such as HRQoL has not yet been explored and will be evaluated in this study by comparing qualitative and quantitative data.

### Sample size considerations

The sample size calculations for this study are based on the primary outcome measure (AQoL instrument). Our pilot research involving people with OA (*n *= 39) showed a mean (SD) improvement in the 6-month AQoL score of 0.04 (0.21) following the ASMP. Given that some of this sample had end-stage joint disease for which conservative management was unlikely to be effective, we expect the effect of the ASMP to be larger than this in people with less severe OA. It is also important to note that the proportion of participants who reported a substantial benefit (an increase in AQoL score of greater than 0.05 utility units) was about 43%, whereas substantial decline occurred in 20% of participants. Using the proportion of people who report an improvement of more than 0.05 AQoL utility units as an outcome, a sample size of 600 (300 participants in each group) will provide sufficient power to detect an additional 10% of participants in the intervention group reporting a minimal important improvement (assuming 30% of control group who report improvement, beta = 0.80, alpha = 0.05, two-tailed).

No data are available on the proportion of people who might experience a clinically important improvement in HRQoL over the study period without receiving the active intervention, although earlier RCTs conducted by the developers of the ASMP have found minimal improvement for no-treatment control groups for up to 1 year (average improvement <2% for pain and <1% for depression) [34,35]. Based on the findings of Solomon et al [19], provision of the arthritis self-management book to the control group in the present study is anticipated to have a negligible impact. However, given the labile nature of OA, it is possible that the control group may experience fluctuations in wellbeing over the study period. Therefore, a 10% advantage for the intervention group is considered to be a conservative estimate of benefit.

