### Planned statistical and qualitative analyses

An intention-to-treat analysis will be performed using all randomised participants who provide any post-baseline data [36].

The intervention and control groups will be examined for baseline comparability with respect to demographic and other factors. Analysis of covariance will be used to assess differences in 12 month outcomes between groups after adjusting for baseline differences. Repeated measures analysis using linear mixed models will assess the constancy of any effects of the ASMP over time.

A cost-utility analysis will be undertaken as part of this research. Standard economic evaluation for clinical trials will be used to assess differences in resource use and health outcomes between groups [37]. The incremental cost or savings per extra person with a clinically significant improvement per Quality-Adjusted Life Year (QALY) compared to the control group will also be calculated. A clinically significant improvement in HRQoL will be regarded as a utility change of at least 0.05 AQoL units [22].

Qualitative analysis techniques will be used for data obtained from the telephone interviews. Interview tapes will be transcribed for analysis; coding of transcripts and any supplementary written notes will be performed using codes developed from the data. Data analysis will be ongoing and will run parallel to the data collection with the objective being to transcribe data from the interview before moving onto the next interview (where feasible). Thematic analysis from the transcripts will be used and results will be discussed according to themes identified from the data.

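### The stated 80% power belongs to a responder proportion, not to the ANCOVA planned for the 12-month AQoL, and the responder comparison itself reaches only about 73% at 300 per group.

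*Protocol article*

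**What the plan says.** Three sections of the protocol article bear on this.

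- **Outcome measures, AQoL instrument:** "The primary outcome for this RCT is HRQoL at 12 months, as measured by the AQoL instrument". The AQoL is a utility score from -0.04 to 1.00. An increase of 0.05 is taken as clinically important.
- **Sample size considerations:** the calculation is said to rest on the primary outcome measure, but it uses a dichotomised form of it: "Using the proportion of people who report an improvement of more than 0.05 AQoL utility units as an outcome". The target is to "detect an additional 10% of participants in the intervention group reporting a minimal important improvement", with 300 per group and "assuming 30% of control group who report improvement, beta = 0.80, alpha = 0.05, two-tailed". (The 0.80 printed as beta can only sensibly be read as power.) The same section gives the pilot result: mean 6-month AQoL change 0.04, SD 0.21, 39 people.
- **Planned statistical and qualitative analyses:** "Analysis of covariance will be used to assess differences in 12 month outcomes between groups after adjusting for baseline differences". A second analysis follows: "Repeated measures analysis using linear mixed models will assess the constancy of any effects of the ASMP over time". In this section the 0.05 responder appears only in the cost-utility paragraph, in an incremental cost for each additional person who improves, where "A clinically significant improvement in HRQoL will be regarded as a utility change of at least 0.05 AQoL units".

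**The concern.** The trial's only power statement is attached to a comparison of two proportions, and the analysis section contains no between-group test of that proportion. The test that is planned, an ANCOVA, has no stated target difference, SD or power. This is more than detail left to a fuller document: the article gives a sizing basis and an analysis method that do not match, while presenting the sizing as based on the primary outcome.

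Power for a responder proportion cannot be read across to a difference in means, because the two depend on different quantities. A reader who takes 80% as the chance of detecting a worthwhile effect is relying on a figure that does not describe the planned analysis. The Discussion ties referral and funding decisions to whether the programme is found effective, so a null result would be interpreted against that figure.

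**Working it through.** All calculations use normal approximations and two-sided alpha 0.05 unless stated.

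**1. The plan's own figure (30% vs 40%, 80% power)**

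n per group = [1.96·√(2·0.35·0.65) + 0.8416·√(0.30·0.70 + 0.40·0.60)]² / 0.10² = (1.3221 + 0.5646)² / 0.01 = 355.9, so **356 per group** (712 in all). With continuity correction it is 376 per group.

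Power at 300 per group: null SE = √(2·0.35·0.65/300) = 0.03894; alternative SE = √(0.45/300) = 0.03873; (0.10 − 1.96·0.03894)/0.03873 = 0.611, so **73%**.

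The stated 300 is not reproduced. A one-sided test with continuity correction does give exactly 300, but the protocol says two-tailed.

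**2. Power for a difference in means**

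Inputs:
- SD of change 0.21: Sample size considerations (pilot, n = 39, 6 months, no control group).
- Between-group difference 0.05: an assumption. The protocol gives 0.05 as an important improvement, not as a target difference between groups. The alternative of 0.04 is the pilot's mean change.
- Correlation r between baseline and 12-month AQoL: not in the document; 0.5 to 0.7 assumed, with baseline AQoL as covariate and equal variance at both times.
- 240 per group: an assumed 20% loss (300 × 0.8).

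If s is the SD at one time point, the SD of change is s√(2(1−r)) and the ANCOVA residual SD is s√(1−r²). Hence residual SD = 0.21·√((1+r)/2), which is 0.1819 for r = 0.5 and 0.1936 for r = 0.7.

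Power = Φ(δ/(SD·√(2/n)) − 1.96), with √(2/300) = 0.08165 and √(2/240) = 0.09129.

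| Difference, n per group | ANCOVA, r = 0.5 | ANCOVA, r = 0.7 | Unadjusted change, SD 0.21 |
|---|---|---|---|
| 0.05, 300 | Φ(3.367−1.96) = 92% | Φ(3.163−1.96) = 89% | Φ(2.916−1.96) = 83% |
| 0.05, 240 | Φ(3.011−1.96) = 85% | Φ(2.829−1.96) = 81% | Φ(2.608−1.96) = 74% |
| 0.04, 300 | Φ(2.693−1.96) = 77% | Φ(2.531−1.96) = 72% | Φ(2.333−1.96) = 65% |

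As r approaches 1 the residual SD approaches 0.21, so for a given SD of change and difference the unadjusted column is a floor for the ANCOVA.

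**3. How firm is the SD?**

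With 38 degrees of freedom and normality assumed, the 95% interval for the SD is 0.21·√(38/56.90) to 0.21·√(38/22.88), about 0.17 to 0.27. Unadjusted power for 0.05 at 300 per group then runs from Φ(0.05/(0.17·0.08165) − 1.96) = 95% down to Φ(0.05/(0.27·0.08165) − 1.96) = 62%. The floor in step 2 is conditional on SD 0.21. None of these figures allows for clustering within course groups.

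**The case against.** The strongest reply is that the mismatch does no harm. On the pilot SD, the planned ANCOVA has more power for a 0.05 difference than the responder test has for 30% against 40%, and the protocol expects an effect larger than the pilot's 0.04. That stands as far as it goes: a reader might infer that the primary test is underpowered, and the documents do not show this. Power falls below 80% only under further assumptions, such as a true difference of 0.04 or a larger SD.

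A reader might also infer that there are two competing primary endpoints, with the choice open until the data are seen. The text does not support that. It names one primary outcome and one between-group method for 12-month outcomes, and in the analysis section the responder serves only the economic evaluation.

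Nor can 0.05 be dismissed as lying within individual noise because it is small beside 0.21. That SD mixes measurement error with real differences in change, the document gives no measurement-error figure, and 0.05 lies inside the minimal important difference range of 0.03 to 0.08 that it cites.

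The differing cuts (more than 0.05 for sizing, at least 0.05 in the economic paragraph) are a wording slip with no demonstrated effect on any result.

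What the reply does not meet is the core point: the only power figure in print describes a test that the analysis section does not contain, and it is also wrong for that test.

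**Conclusion.** The concern holds in this form. The stated 80% is not the power of the planned ANCOVA, and for the responder comparison on which it was calculated the figure is about 73% at 300 per group, against 356 per group needed. Both statements follow from the protocol's own inputs.

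The power of the ANCOVA is indicative only. It is about 89% to 92% for a 0.05 difference with complete data, 81% to 85% at 240 per group, and 72% to 77% for 0.04 at 300 per group. These values rest on an uncontrolled 6-month SD from 39 people and on assumed values for the target difference, correlation and loss. They do not establish a shortfall, and they do not establish that the size is comfortable.

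**What to change.** - In the analysis section, state that the primary analysis is the baseline-adjusted mean difference in AQoL at 12 months, estimated by ANCOVA.
- In the sample size section, replace the responder-based statement with one for that ANCOVA. Give the target difference, SD, correlation, allowance for loss and two-sided alpha, and show a range rather than one value. The table above can serve, with the unadjusted 83% (300 per group) and 74% (240 per group) as the conservative end for a 0.05 difference and SD 0.21, and with the 0.04 row shown beside it. Mark the difference, correlation and loss as assumptions and the SD as a pilot estimate.
- Label the responder comparison as secondary, use one cut definition throughout, and do not attach the 80% to it. If its power is reported, it is about 73% for 30% against 40% at 300 per group.
- Print 0.80 as power, not beta.

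The cost is rewording two paragraphs. No extra participants or data are needed for this change. The authors do have to commit to a target mean difference, which the article does not now state.

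### Under its own inputs (30% v 40% responders, two-sided 5%), 300 per group gives about 73% power, not 80%

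*Protocol article*

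**What the plan says.** The Sample size considerations section bases the calculation on the AQoL instrument, the primary outcome measure, but sizes the trial on a binary version of it: "Using the proportion of people who report an improvement of more than 0.05 AQoL utility units as an outcome". It then claims that "a sample size of 600 (300 participants in each group) will provide sufficient power to detect an additional 10% of participants", and gives the remaining inputs in brackets: "assuming 30% of control group who report improvement, beta = 0.80, alpha = 0.05, two-tailed".

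Nothing in that section allows for loss to follow-up. The Abstract and the section on identification and recruitment give the same 600 as the number to be recruited. The planned analyses section defines the analysis set as follows: "An intention-to-treat analysis will be performed using all randomised participants who provide any post-baseline data".

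**The concern.** The calculation is closed: endpoint, both proportions, group size, alpha, sidedness and target power are all printed, so nothing is left for a fuller protocol or an analysis plan to supply. The stated result can therefore be checked directly, and 300 per group looks too few for a 10-point difference from 30% at two-sided 5% with 80% power.

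The label is also wrong. Beta is the type II error rate, so a beta of 0.80 read literally means 20% power. The intended meaning must be power of 0.80.

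What is at stake is how a null result would be read. The Discussion says that if the program is not found effective, resources could go elsewhere. A reader who takes the stated power at face value would put the chance of missing a true 10-point advantage at 20%, when it is about 27% with complete follow-up.

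**Working it through.** **Inputs**, all from Sample size considerations:
- control proportion p1 = 0.30 ("assuming 30% of control group who report improvement")
- intervention proportion p2 = 0.30 + 0.10 = 0.40 ("an additional 10% of participants in the intervention group reporting a minimal important improvement")
- n = 300 per group, 1:1
- alpha 0.05 two-sided, power 0.80 ("beta = 0.80, alpha = 0.05, two-tailed", with beta read as power)

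Derived: mean proportion 0.35, so 2 × 0.35 × 0.65 = 0.455; p1(1−p1) + p2(1−p2) = 0.21 + 0.24 = 0.45. Normal quantiles: 1.96 (two-sided 5%), 0.8416 (80% power).

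**Attempt to reproduce the stated size.** The usual pooled two-proportion formula is

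n = [1.96 √0.455 + 0.8416 √0.45]² / 0.10² = (1.3221 + 0.5646)² / 0.01 = 355.9, so 356 per group (712 in total).

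Other two-sided methods:

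| Method | n per group for 80% power | Power at 300 per group |
|---|---|---|
| Pooled variance | 356 | 72.9% |
| Unpooled variance | 354 | 73.3% |
| Arcsine | 356 | 73.0% |
| Continuity-corrected | 376 (752 in total) | 70.0% |
| Exact enumeration of the pooled z-test | not computed | 73.1% |

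None gives 300 per group or 80%. The gap of 54 to 76 per group is too large for rounding.

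**Power at the stated size**, pooled formula:

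Φ[(0.10 − 1.96 √(0.455/300)) / √(0.45/300)] = Φ[(0.10 − 0.0763) / 0.0387] = Φ(0.611) = 0.729.

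**Where 300 may come from.** With a one-sided 5% test, 80% power needs 281 per group without continuity correction and exactly 300 with it; power at 300 is 82.3% and 80.0% respectively. A one-sided calculation reported as two-tailed is therefore a plausible source, but this is inference and the finding does not depend on it.

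**Difference detectable with 80% power.** Solving the pooled formula for p2 with p1 = 0.30 gives 10.9 points at 300 per group (30% v 40.9%).

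**Sensitivity to missing 12-month AQoL.** The loss rates here are assumed; the article gives none.

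| Loss | n per group | Power, 30% v 40% |
|---|---|---|
| 10% | 270 | 68.4% |
| 15% | 255 | 65.9% |
| 20% | 240 | 63.3% |

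At 240 per group the detectable difference with 80% power is 12.3 points.

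**The case against.** The strongest reply is that the responder comparison is not the planned primary test. The primary outcome is AQoL at 12 months, and the planned analyses section compares 12-month outcomes by analysis of covariance; within that section the 0.05 threshold appears only in the cost-utility paragraph. Suppose the pilot SD of change, 0.21, held in both groups (an assumption, from 39 people followed for 6 months). The standard error of a difference in means at 300 per group is then 0.21 √(2/300) = 0.0171, and power for a 0.05 difference is Φ(0.05/0.0171 − 1.96), about 83%. That point stands as a limit on the harm: the article does not show that the primary comparison is underpowered. It does not rescue the sentence, because the article makes its power claim for the responder proportion alone. The same assumption gives about 65% power for a difference of 0.04, the size of the pilot's own mean improvement, and about 74% for 0.05 with 240 per group.

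Two further objections have some force. First, a condensed article may leave a dropout allowance to the full protocol, so its absence is not counted as an error here; the loss figures are sensitivity information only. Second, the pilot's 43% improvers might suggest a larger effect, and 30% v 43% would have about 91% power at 300 per group. That pilot figure is uncontrolled and small, and the article chose to power for 10 points.

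The beta label is a slip with a clear meaning and would carry little weight alone.

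**Conclusion.** The concern holds. On the printed inputs, 300 per group gives 73% power (70% with continuity correction), and 80% would need 356 per group (376 with continuity correction). This rests on no outside assumption beyond reading the printed beta as power, and it is true with no loss to follow-up. Any loss lowers power further, by an amount that depends on a rate the article does not give. The conclusion is confined to the responder comparison used for sizing and says nothing definite about the power of the analysis of covariance.

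**What to change.** Keep 600 and restate the claim in Sample size considerations, for example: *With 300 per group the trial has 73% power (two-sided alpha 0.05) to detect 30% v 40% responders; the difference detectable with 80% power is 10.9 percentage points.* Wherever the 80% figure is kept, write *power = 0.80 (beta = 0.20)* in place of the present label.

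If the sponsor wishes to show the effect of missing 12-month AQoL scores, it should add a clause using its own expected rate; at 20% missing, the detectable difference would be 12.3 points.

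The cost is wording only: a slightly less favourable stated figure, with no extra participants and no change to the design.
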